# Leukocyte- and platelet-rich fibrin in cranial surgery: study protocol for a prospective, parallel-group, single-blinded randomized controlled non-inferiority trial {1}

**DOI:** 10.1186/s13063-023-07252-w

**Published:** 2023-03-23

**Keywords:** CSF leakage, Dura, Sealing, Prevention

## Abstract

**Background:**

CSF leakage is a major complication after cranial surgery, thus, adequate dural closure must be performed. Commercially available fibrin sealants are currently considered the gold standard for dural closure, but problems have been reported regarding safety, efficacy, and costs. This trial aims to investigate autologous leukocyte- and platelet-rich fibrin (L-PRF) as an alternative to commercially available fibrin sealants.

**Methods/design:**

This single-blinded, prospective randomized controlled interventional trial aims to demonstrate the non-inferiority of L-PRF compared to commercially available fibrin sealants for dural closure. This trial will include patients undergoing cranial neurosurgery (supratentorial and infratentorial) with intentional opening of the dura. Patients are randomized in a 1:1 fashion comparing L-PRF to commercially available fibrin sealants. The primary endpoint is postoperative CSF leakage within 12 weeks after surgery. Secondary endpoints are complications such as bleeding or wound infections. Additionally, a cost-effectiveness analysis is performed.

**Discussion:**

With this trial, we will evaluate the safety and efficiency of L-PRF compared to commercially available fibrin sealants.

**Trial registration:**

ClinicalTrials.gov NCT03812120. Registered on 22 January 2019.

**Supplementary Information:**

The online version contains supplementary material available at 10.1186/s13063-023-07252-w.

## Administrative information

We used the Standard Protocol Items: Recommendations for Interventional Trials (SPIRIT 2013) checklist when writing our report [1]. The numbers in curly brackets in this protocol correspond to the SPIRIT checklist item numbers.

**Table Taba:** 

Title {1}	Leukocyte- and platelet-rich fibrin in cranial surgery: a prospective, randomized controlled trial
Trial registration {2a}	Clinicaltrials.gov (ID: NCT03812120) KU/UZ Leuven: S61460
Protocol version {3}	V8 dd 9–12-2021
Funding {4}	FWO TBM grant T003018N
Author details {5a}	Experimental Neurosurgery and Neuroanatomy, Department of Neurosciences, KU Leuven, Leuven, Belgium Department of Neurosurgery, UZ Leuven, Leuven, Belgium
Name and contact information for the trial sponsor {5b}	UZ Leuven [name] [name]
Role of sponsor {5c}	The sponsor has no role in the design of the study, study conduct, collection of the data, analysis, or writing of trial manuscripts
Date and version identifier {3} Date	Version
7–11-2018	Original (v1)
19–9-2019	Amendment no.1: Sample size correction, added detail to inclusion and exclusion criteria (v4)
5–2-2020	Amendment no.2: Addition of ICF translated in French and English (v4)
15–12-2020	Amendment no.3: Addition of quality control measures (v6)
24–11-2021	Amendment no.4: Specification of quality control measures (v8)

## Background {6}

A common complication after cranial surgery is cerebrospinal fluid (CSF) leakage. Our recently published systematic review, summarizing data from 113 studies, showed an average postoperative CSF leakage rate of 2.9% in supratentorial procedures, 5.8% in infratentorial procedures, and 4.1% in endoscopic transsphenoidal surgeries. Postoperative leaks may require revision surgeries and/or external CSF drainage [2]. Adequate dural closure is necessary to prevent CSF-related complications such as infection and intracranial hypotension. Currently, commercially available fibrin sealants are considered the gold standard for dural closure, due to their hemostatic, adhesive, and sealant properties. However, problems regarding efficacy, cost, and safety have been reported.

A possible alternative to commercially available fibrin sealants is autologous fibrin rich in platelets and leukocytes. The technique to produce such fibrin membranes was first described by Choukroun et al. in 2001 [3]. Leukocyte- and platelet-rich fibrin (L-PRF) is currently applied as an autologous biomaterial in various specialties, including oral and maxillofacial surgery and sports medicine [4]. The main advantage of L-PRF is that it is completely autologous, thereby minimizing the risk of immunological reactions. L-PRF is readily available as it is derived from the patient’s own blood, and accordingly, the method for preparation is non-invasive. Finally, L-PRF can be prepared “bedside” during surgical procedures by the operating room staff, within a 20-min time frame. For L-PRF membrane preparation, blood is collected in glass-coated tubes and centrifuged at 400* g* for 12 min (Fig. 1). During centrifugation, platelets are activated and the coagulation cascade is initiated. This results in a fibrin clot, which can be compressed into a membrane, for use as an onlay graft or cylinder to plug defects. These flaps can be placed on a defect, where the leukocytes and platelets that are incorporated in the fibrin network deliver growth factors to the surrounding tissue. Analogously, liquid L-PRF glue can be prepared in plastic-coated tubes. Because of the hydrophobic surface and shorter centrifugation time (3 min), the product maintains its native fibrinogen and only coagulates in contact with other tissues [5].

**Fig. 1 Fig1:**
[figure not shown]
Leukocyte- and platelet-rich fibrin (L-PRF) preparation protocol. Top: membrane preparation after blood collection in glass tubes and centrifugation for 12 min (400 g), compression of the fibrin clot. Bottom: liquid L-PRF glue preparation after blood collection in plastic tubes and centrifugation for 3 min (400 g), collection of the upper layer in a sterile syringe

Application of L-PRF would improve wound healing and tissue regeneration, with a reduced infection risk. Apart from the uncomplicated preparation process, the low cost is an additional benefit of L-PRF. The cost of 8 blood tubes is approximately €12, which is very low compared to the price of commercially available fibrin sealants (€100–250) [6].

Given the myriad of theoretical advantages, the use of L-PRF is currently studied in numerous medical disciplines. In neurosurgery, it could play a role in the watertight closure of the dura. The application of L-PRF, in particular, in skull base reconstruction after endoscopic endonasal approaches, has already been described in a few retrospective research articles [7–9]. No major contra-indications were reported for L-PRF in endoscopic endonasal skull base reconstruction or craniectomies. Although L-PRF was reported as a promising biological, studies thus far concluded that larger, prospective trials are warranted to explore the possible applications of L-PRF. This clinical study aims to provide evidence in support of L-PRF in dural closure.

## Objectives {7}

The general aim of this study is to evaluate the potential of L-PRF in dural closure. More specifically, we are investigating L-PRF as an onlay graft on sutured dura in supratentorial and infratentorial surgeries. We aim to show the non-inferiority of L-PRF compared to the current standard practice. In addition, we want to demonstrate that L-PRF is more cost-effective than standard commercially available fibrin sealants. Risk factors and possible complications will be evaluated to validate safety.

## Trial design {8}

This study is a single-blinded, prospective randomized controlled trial with subjects randomized 1:1 in two parallel groups, i.e., experimental (L-PRF treatment) and active control (commercially available fibrin sealants).

In this study, the general objective is to show the non-inferiority of L-PRF as a closure technique compared to commercially available fibrin sealants in supra- and infratentorial surgery. This prospective randomized controlled trial was approved by the local Ethical Committee (UZ Leuven, S61460) and is registered at ClinicalTrials.gov (ID: NCT03812120) [2]. Recruitment started on 06 January 2020.

Demographic data, medical history, and surgical indications are reported prior to surgery. During the hospitalization (from 1 day preoperatively until the day of discharge), vital parameters such as body temperature and blood pressure are monitored, as well as medication intake. Patient’s quality of life (QoL) is questioned using the Research and Development 36-item Short Form Survey (RAND SF-36) and EuroQol Five Dimensions (EQ-5D) questionnaires.

To perform a cost-effectiveness evaluation, all costs and effects will be collected. Additionally, patient’s general quality of life is assessed using the EQ-5D-3L Questionnaire prior to surgery and at the 6–12 weeks follow-up visit (FU3). Complications and adverse events are assessed at the time of surgery, 2 days postop (FU1), at hospital discharge (FU2), and at follow-up visits (FU3) (Fig. 2).

**Fig. 2 Fig2:**
[figure not shown]
Flowchart of “L-PRF in cranial surgery, a prospective randomized controlled trial.” After obtaining informed consent, patients are screened and asked to complete quality of life (QoL) questionnaires (EQ-5D and RAND SF-36). During surgery (i.e., before dural closure), study subjects are randomized into the experimental arm (L-PRF) and the control arm (commercially available fibrin sealants). During hospitalization, patients are followed up with clinical controls after 2 days (FU1) and on the day of discharge (FU2). One outpatient follow-up is done between 6 and 12 weeks postop (FU3), with MRI imaging and completion of the QoL questionnaires

## Methods: participants, interventions, and outcomes

### Study setting {9} and participants {10}

This study is recruiting patients admitted to the Department of Neurosurgery of the University Hospitals Leuven (UZ Leuven) for elective neurosurgical procedures. Before initiation of any study procedure, participants (or their legal representative) must provide written informed consent (Additional file 2: Appendix 1). Inclusion criteria are patients undergoing cranial surgery with intentional opening of the dura (supratentorial and infratentorial approach) with a minimum age of 18 years (Table 1). Surgical indications include tumor resection and vascular (aneurysm, arteriovenous malformations) or functional (epilepsy surgery, microvascular decompression) neurosurgery. Pregnancy and participation in other clinical trials with study drugs or devices are exclusion criteria. Patients undergoing transsphenoidal surgery for sellar or parasellar lesions are not included, as we are currently performing a similar study on this subject, with more appropriate clinical follow-up for that type of lesion.

**Table 1 Tab1:** Eligibility criteria

Inclusion criteria	Exclusion criteria
Age ˃ 18 years	Age ˂ 18 years
Supratentorial or infratentorial surgery	Transsphenoidal surgery
Informed consent signed	Pregnancy
	Participation in other clinical studies with drugs or medical devices

### Who will take informed consent? {26a}

Patients will be informed about the study by the neurosurgeon at the moment the elective surgery is planned. The information brochure is sent in advance by the study coordinator. Informed consent is obtained by trained study staff prior to surgery, i.e., on the day of hospital admission, usually 1 day before surgery. Specialized forms for interpreters are available, as well as specialized informed consent forms for patients not capable to give consent (legally authorized representative). In such cases, an individual’s capacity to consent is determined by the physician.

### Additional consent provisions for collection and use of participant data and biological specimens {26b}

There are no plans for additional studies using the data collected in this trial. No biological specimens are collected.

## Interventions

### Explanation for the choice of comparators {6b}

At present, commercially available fibrin sealants are considered the gold standard for dural closure. At UZ Leuven, Tisseel® (Baxter, Deerfield, IL, USA) and TachoSil® (Corza, Düsseldorf, Germany) are used as the standard of care for dural closure. Tachosil® is approved by the European Medicines Agency (EMA) and Food and Drug Administration (FDA) for this indication.

### Intervention description {11a}

The surgery is performed by a team of trained neurosurgeons according to local standards. The dura is primarily closed with sutures, and additional grafts can be used to close the remaining defects. For patients allocated to treatment with L-PRF, no commercially available fibrin sealants may be used for dural closure, but they can be used for hemostasis or to fixate Teflon® or vessels during microvascular decompression. Additional autologous (pericranium, muscle, fat grafts), allogenic (fascia lata), or synthetic (NeoDura®, Medprin Biotech GmbH, Frankfurt am Main, Germany) materials and hemostatic materials (cellulose sponges such as Spongostan® (Ethicon Biosurgery, Johnson and Johnson, New Brunswick, NJ, USA), Floseal® (Baxter, Deerfield, IL, USA), or Surgicel® (Ethicon Biosurgery, Johnson and Johnson, New Brunswick, NJ, USA)) can be used in both groups if deemed necessary by the surgeon.

L-PRF and liquid L-PRF glue are prepared during surgery. In all study subjects, L-PRF preparation is performed by the study coordinator to ensure protocol adherence. In this procedure, timing is particularly important to guarantee optimal membrane formation. Therefore, the arterial line is flushed, and immediately after, 20 mL of arterial blood is collected in a sterile syringe and transferred to two sterile 10-mL glass tubes (A-PRF®, Process for PRF, Nice, France), and instantaneously put in a centrifuge at 2700 rpm (400* g*) (IntraSpin®, Intra-Lock, Boca Raton, FL, USA). At the time of transfer to the glass tubes and start of centrifugation, a second 20-mL syringe is filled with arterial blood. The centrifugation process is interrupted as the second batch of collected blood is transferred to 10-mL glass tubes, to ensure precise timing to add the tubes into the centrifuge when decelerated. The centrifuge is instantly restarted at 2700 rpm for 12 min. If deemed necessary, one more 20-mL syringe can be collected to fill two more 10-mL glass tubes and added to the centrifuge in a similar fashion. After the centrifugation process, the tubes are inspected for the presence of a dense clot right above the red blood cell layer. If these are not present, the tubes are set aside for 10 min and inspected again. The tubes are opened and presented to the scrub nurse to remove the clot with sterile tweezers. The clot is placed in an Xpression Box® (Intra-Lock, Boca Raton, FL, USA) and gently compressed by placing the compression plate and the lid on top. After 5 min, the membranes are ready for surgical application by placing them on sutured dura. If necessary, the membranes can be left in the Xpression box® for up to 3 h until application.

Liquid L-PRF glue is prepared in a similar fashion. The arterial line is flushed, and 20 mL of blood is collected in a sterile syringe. The blood is then transferred to plastic tubes (S-PRF®, Process for PRF, Nice, France) and placed in the centrifuge for 3 min (2700 rpm/400* g*). If necessary, an additional 20 mL can be collected for liquid L-PRF glue preparation. After centrifugation, the tubes are opened and presented to the scrub nurse. The yellow upper layer is aspirated into a sterile syringe using a large-gauged transparent catheter-over-needle. Liquid L-PRF glue can be directly applied on L-PRF membranes placed on the dura. Alternatively, cellulose sponges or bone fragments can be immersed in the liquid L-PRF glue before placing them on the defect.

### Criteria for discontinuing or modifying interventions {11b}

After allocation to the experimental or control arm, the patient can still be excluded from the study in certain cases, specified as the perioperative exclusion criteria. A patient allocated to the control arm may be excluded if there is a clear indication for hypersensitivity reactions to commercially available fibrin sealants. Patients allocated to L-PRF may be excluded if the L-PRF preparation process fails or if the product is considered of insufficient quality. Subjects with other intraoperative findings identified by the surgeon that may preclude the conduct of the study procedure can be excluded as well, to ensure optimal patient care in the situation. For example, when the dura is exceptionally damaged, the surgeon may opt for multilayer reconstruction using multiple grafts, commercially available sealants, and autologous materials. Study participants can withdraw from the study at any moment, which implies all subsequent study procedures and data collection are discontinued.

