### Sample size {14}

Sample size calculation was performed according to the primary outcome, using an online power calculator for binary outcome non-inferiority trials (Sealed Envelope Ltd. available from: www.sealedenvelope.com). This is a non-inferiority trial with a binary outcome using a one-sided alpha of 0.05 and 80% power. The assumed success rate is 93.7% in the control arm, based on center-specific experience as well as the literature [13]. Data on the use of L-PRF for this indication is limited, but we assume a 95% success rate based on a prior feasibility study [9].

The statistical hypothesis for testing the treatment difference is presented as follows: H_0_: Δ ≤  − 0.05 tested against the alternative hypothesis and H_A_: Δ >  − 0.05, where Δ is the difference between the success rates of experimental and control condition and − 0.05 is the non-inferiority difference. The non-inferiority limit was set at 0.05 considering (1) reported CSF leakage rates without commercially available fibrin sealant averaging 17.2% [14] and (2) important additional benefits of L-PRF compared to commercially available fibrin sealants including the completely autologous nature (eliminating immune reactions), presence of immunologic cells and reduced costs.

Based on this power calculation, 334 patients need to be included, 167 in each group. A drop-out rate of 2–5% is expected due to loss of follow-up and non-adherence to the allocation or failure of L-PRF preparation. Therefore, 350 patients will be enrolled, 175 in each group.

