### Methods in analysis to handle protocol non-adherence and any statistical methods to handle missing data {20c}

The results will be analyzed according to the “intention-to-treat” (all randomized participants, irrespective of protocol adherence), “per-protocol” (only participants that were treated according to the protocol), and “as-treated” (all participants according to the treatment they received) principles. These three analyses will be compared to show the possible impact of a lack of data on the results. For the primary endpoint, no missing data are expected. For secondary endpoints (cost-effectiveness evaluation), the predictive mean of the other values within the arm will be used.

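### Exclusion from the study after allocation, on partly arm-specific grounds, conflicts with the promised all-randomised ITT analysis and can bias the trial towards non-inferiority

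*Protocol article*

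**What the plan says.** **Exclusion after allocation.** Criteria for discontinuing or modifying interventions {11b} gives three grounds on which an already allocated patient can be taken out of the study:

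- L-PRF arm only: "Patients allocated to L-PRF may be excluded if the L-PRF preparation process fails or if the product is considered of insufficient quality".
- Control arm only: a clear indication of hypersensitivity to commercial fibrin sealant.
- Either arm: intraoperative findings that, in the surgeon's view, rule out the study procedure. The example is that "when the dura is exceptionally damaged, the surgeon may opt for multilayer reconstruction", and commercial sealants are among the materials named.

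**Drop-out.** Sample size {14} says that a drop-out of 2–5% "is expected due to loss of follow-up and non-adherence to the allocation or failure of L-PRF preparation", and raises the total from 334 to 350 for it.

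**Analysis sets.** Item {20c}, on non-adherence and missing data, defines ITT as everyone randomised, whatever their adherence. It adds a per-protocol and an as-treated set and expects no missing primary data. Of the three sets it says: "These three analyses will be compared to show the possible impact of a lack of data on the results".

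**Who knows the arm.** Under Who will be blinded? {17}, surgical staff are not blinded. The arm is announced after dural opening, hence before closure. Intervention description {11a} bars commercial sealant for dural closure in the L-PRF arm only; in the control arm it is the assigned treatment.

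**The concern.** A patient who has been taken out of the study and covered by the drop-out allowance is not available to an analysis of everyone randomised. Items {11b} and {14} point one way and item {20c} the other. A later analysis plan can choose between sets, but it cannot recover outcomes that were not collected.

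The exclusions also happen once the arm is known, and they are not symmetrical. Failed preparation is part of how the L-PRF strategy performs, yet it can remove patients only from that arm. The damaged-dura ground is worded for both arms, but it can act unequally: closing with commercial sealant departs from the allocation in the L-PRF arm and not in the control arm.

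At stake is the false-claim rate of the non-inferiority test. If patients at high risk of a leak are removed mainly from L-PRF, the apparent deficit shrinks. If an L-PRF patient closed with sealant is regrouped as control in the as-treated set, that patient's leak counts against the comparator. Comparing adherence-based sets also does not show what missing outcomes do to the result, which is the purpose item {20c} gives for it.

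**Working it through.** **1. The plan's own figure.** Inputs from Sample size {14}: "using a one-sided alpha of 0.05 and 80% power"; "The assumed success rate is 93.7% in the control arm"; "we assume a 95% success rate based on a prior feasibility study"; "The non-inferiority limit was set at 0.05".

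n per arm = (1.645 + 0.842)² × (0.937×0.063 + 0.95×0.05) / (0.95 − 0.937 + 0.05)² = 6.183 × 0.10653 / 0.003969 = 165.9, so 166 per arm and 332 in total, against 334 stated. The figure reproduces.

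Drop-out: 334/0.98 = 341 and 334/0.95 = 352. The planned 350 covers 1 − 334/350 = 4.6%. Power on the plan's rates is 81.8% with 350 analysed and 80.2% with 334. The sample-size arithmetic is sound; the problem lies in the analysis population.

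**2. How many patients.** 2–5% of 175 is about 4 to 9 patients. The plan's 5% leak rate gives about 9 leaks in the whole L-PRF arm (0.05 × 175 = 8.75).

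**3. Error rate at the margin.** Control leak risk is 6.3%. True L-PRF leak risk is 6.3% + 5% = 11.3%, with 175 per arm. A share f of the L-PRF arm has leak risk q.

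- *Dropped:* retained L-PRF leak risk = (0.113 − f·q)/(1 − f), with n = 175(1 − f). The control arm is unchanged.
- *As-treated:* the same patients are counted as control, whose leak risk becomes (0.063 + f·q)/(1 + f), with n = 175(1 + f).
- Error = Φ[(difference in success + 0.05)/SE − 1.645], SE unpooled.

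The documents do not give q, so it is an **assumption** shown over a range: 6.3% is the control rate, 11.3% the L-PRF arm average in this scenario, 17.2% the rate without sealant cited in Sample size {14}, and 30–40% has no source in the documents. The share f = 2–5% is an upper range, because that figure is total drop-out and includes ordinary loss to follow-up.

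Example with f = 0.05 and q = 0.172:

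- Dropped: (0.113 − 0.0086)/0.95 = 0.1099; difference 0.063 − 0.1099 = −0.0469; SE 0.0304; Φ(0.102 − 1.645) = 6.1%.
- As-treated: control leak (0.063 + 0.0086)/1.05 = 0.0682; difference −0.0417; SE 0.0306; Φ(0.272 − 1.645) = 8.5%.

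| Assumed leak risk q | Dropped, f = 2–5% | As-treated, f = 2–5% |
|---|---|---|
| 6.3% | 4.7–4.2% | 4.7–4.2% |
| 11.3% | 5.0% | 5.3–5.9% |
| 17.2% | 5.4–6.1% | 6.2–8.5% |
| 30% | 6.5–9.4% | 8.6–17.0% |
| 40% | 7.4–12.9% | 10.9–26.7% |

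With everyone analysed as allocated, the error is 5.0%. With f = 1%, dropping gives 5.2% at q = 17.2% and 6.1% at q = 40%. If the two-sided 95% interval of item {20a} decides, the nominal error is 2.5%. Dropping 2–5% then gives 2.7–3.2% at q = 17.2% and 3.3–7.4% at q = 30–40%.

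**The case against.** The strongest reply is that the text allows a harmless reading. Item {11b} says that data collection stops for participants who withdraw; it does not say so for perioperative exclusions. Complications come from hospital databases (Outcomes {12}) and follow-up data from the electronic files (item {18a}), so the primary endpoint may still be obtainable. On that reading, excluded patients leave only the per-protocol set. This stands in part: a reader might infer that these patients are lost before 12 weeks, and the documents do not state it. But exclusion from the study, together with their place in the drop-out allowance, is hard to square with this reading, and nothing in the article settles it.

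A reader might also infer that the exclusions do bias the trial towards L-PRF. The documents do not support that. The direction depends on the excluded patients' leak risk, which is not given. A patient whose clot failed and who was closed with sealant could plausibly carry the control risk of 6.3%, and then the bias reverses slightly. High risk is plausible for badly damaged dura, but that ground is open to both arms and the control arm has a ground of its own.

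The as-treated set is worse only if the regrouped patients carry more than the control risk. It is one of three sets, and nothing says that it decides. Naming the deciding set is largely a matter for the analysis plan, which is not shown, so its absence is not counted as an error here.

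**Conclusion.** The conflict is in the text. Items {11b} and {14} remove allocated patients and count them as drop-out, while item {20c} promises all randomised patients and a complete primary endpoint. They must be reconciled, because the primary comparison depends on who is in it.

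The effect on the result is a possible bias of uncertain size. Up to the highest leak rate in the documents (17.2%), dropping 2–5% of the L-PRF arm moves the 5% error to at most 6.1%, and as-treated regrouping moves it to at most 8.5%. Larger values, up to 12.9% and 26.7%, need an assumed leak risk of 30–40% and the whole drop-out allowance falling on such L-PRF patients. They show what is possible and are not an estimate. All figures assume a true deficit exactly at the margin, no exclusions from the control arm and a normal approximation.

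**What to change.** In item {11b}, replace exclusion from the study by wording such as: *allocated technique not applied; the patient stays in the study, is followed to 12 weeks for the primary endpoint and is analysed in the allocated arm, unless consent is withdrawn.* The surgeon's choice of closure stays as it is.

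Use these events only to define the per-protocol set, and report them by arm and reason. Preferably, base the non-inferiority claim on ITT supported by per-protocol, and label as-treated as descriptive. Drop the statement that comparing the three sets shows the impact of missing data.

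Keep the drop-out allowance. Failed preparations and non-adherence still shrink the per-protocol set, and the allowance protects its power. In Sample size {14}, describe them as losses to that set and not as losses from the study.

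The cost is a short amendment and about 4 to 9 L-PRF patients at most (plus any in the control arm) to follow through visits already scheduled. The required number does not rise. The drawback is that L-PRF failures closed with sealant and kept in the L-PRF arm may move the ITT estimate either way: they add leaks if they are high-risk, or dilute a true difference if sealant protects them. This is why per-protocol is read alongside ITT.
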